
Unfortunately, the high methodological confounds of some of the previous studies and knowledge gaps lead to little evidence regarding the effectiveness of CT to improve the biochemical and immune markers of metabolic disease, lung function, quality of life, and stress in sedentary adult office workers. So, new studies are required to improve the quality of evidence on this topic. This trial aims to analyse the effects of a 16-week CT program on metabolic disease risk markers, including inflammatory cytokine profile, markers of IR (fasting glucose and insulin levels, HOMA-IR), leptin and adiponectin levels (as surrogate markers of adipose tissue dysfunction), lung function, salivary stress hormones and subjective quality of life (primary outcomes), as well as body composition and physical fitness (secondary outcomes), in sedentary middle-aged office workers of both genders. Furthermore, we aimed to assess the associations between the changes promoted by the exercise intervention and the different variables studied.

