## Materials and methods

### Study design and setting

This trial is designed as a single-blinded two-arm randomized controlled trial (RCT) with parallel groups, and an allocation ratio of 1:1. Fig 1 illustrates the overall study. This study protocol follows the SPIRIT Statement guidelines for standard protocol items in clinical trials [46] and is registered in the Clinicaltrials.gov ID: NCT04868240 (date of registration April 30, 2021). This RCT study has been designed and results will be reported according to the Consolidated Standards of Reporting Trials (CONSORT) statement [47]. Furthermore, and since that exercise training interventions are not properly and completely addressed by the CONSORT checklist [48], the guidelines of the Consensus on Exercise Reporting Template (CERT) will also be considered [49].

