### Participants

In this RCT, a minimum of 40 office-workers aged 40–64 years will be recruited, enrolled, and randomized (n = 20 per group). Potential eligible subjects will be recruited from two office companies in Coimbra city, Portugal. The principal investigator (PI) of this project will meet with the directors/leaders of these companies to present and discuss the purposes and procedures of this research project. Afterwards, a poster will be disseminated on their internal web pages and the subjects will be able sign up online or by telephone. Interested subjects will receive information about the study and will be pre-screening for initial eligibility criteria through telephone/online interviews. The subjects ruled eligible will be invited for an in-person screening visit where they learned more about the study, sign the informed consent form, and complete additional screening measures. Lastly, the subjects that meet all the defined eligibility criteria will be invited to return for a baseline assessment visit. After the baseline assessments, participants will be randomized and notified by email/telephone (by the PI).

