### Estimated sample size

The sample size was calculated using a priori power analysis through the G*Power software version (3.1.9.2.), following the guidelines of Faul et al. [54]. For an effect size of 0.30, a sample size of 20 participants per group achieves 95% power to detect differences among the means versus the alternative of equal means using an F test with a 5% α-level. This analysis indicated a minimum total sample size required in this study. We plan to enrol 20% more persons to account for dropouts.

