### Data analysis

Data analyses will be performed using SPSS Statistics version 25.0 (SPSS Inc., IBM Company, Chicago, Illinois, USA). Descriptive statistics (mean ± SD) will be performed for all variables in the analysis. The assumption of normality will be tested using histograms, normal probability plots and Shapiro-Wilk test. Chi-squared test will be performed to analyse sex proportions between groups. Assuming data normality, a two-way analysis of variance (ANOVA) for repeated measures will be applied for intra- and inter-group comparisons. In absence of normality, non-parametric Kruskall-Wallis test will be used. Bonferroni’s *post hoc* test will be performed if significant differences exist (alpha level set at 0.05). The magnitude of the global effect size will be calculated using Cohen’s effect size [104]. The Cohen’s d effect size is categorized according to the following criteria: *d* = < 0.20 (small), 0.21–0.79 (medium) and > 0.80 (large) [104]. The bivariate associations between the changes promoted by the exercise program and the different variables studied will be assessed by Spearman’s rank and Pearson’s coefficients. The strength of the associations will be classified as follows [105]: very high (0.90 < r < 1.00); high (0.70 < r < 0.90); moderate (0.50 < r < 0.70); low (0.30 < r < 0.50); little (0.10 < r < 0.30). Significance level set at *p* ≤ 0.05.

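### The post hoc trigger and the conclusion are not tied to group-by-time, so a change shared by both arms can give a significant training-arm result that does not test the programme

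*Protocol article*

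**What the plan says.** The aim, at the end of the Introduction, is causal: "This trial aims to analyse the effects of a 16-week CT program on metabolic disease risk markers", followed by lung function, stress hormones and quality of life. The design is a two-arm parallel randomised trial with "an allocation ratio of 1:1".

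The Data analysis section states that, under normality, "a two-way analysis of variance (ANOVA) for repeated measures will be applied for intra- and inter-group comparisons". It adds that a Bonferroni post hoc "test will be performed if significant differences exist (alpha level set at 0.05"). The section closes with "Significance level set at" p ≤ 0.05.

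A two-way repeated-measures ANOVA gives three F tests: group, time and group-by-time. The section does not say which of them opens the post hoc tests, or which supports a conclusion about the programme. The group-by-time interaction is not mentioned anywhere in the article.

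Table 3 sets the number of visits. Blood and saliva are sampled before and after the programme only. Body composition, fitness, spirometry, quality of life and blood pressure are also measured at week 8.

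**The concern.** The trial asks whether the programme changes outcomes, so the relevant null hypothesis is equal change in the two arms. The time effect and the pre-post comparison inside the training arm test another null: that nothing changes over 16 weeks. That null is false whenever both arms move together, for instance through practice on a repeated test or through season, even if the programme does nothing.

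Intra-group comparison is a named purpose of the ANOVA and the trigger is unrestricted, so a significant time effect satisfies it. The follow-up can then show a significant change in the training arm, sometimes with none in the control arm. Significance in one arm and not in the other is not a test of the difference between arms. The Bonferroni adjustment covers the number of pairwise comparisons and does not alter which null is tested.

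What is at stake is the benefit of having a control group. The Introduction lists the lack of one among the weaknesses of earlier studies, and a pre-post test in the training arm shares that weakness.

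**Working it through.** **Does the sample-size statement show which term was meant?** The plan says "For an effect size of 0.30, a sample size of 20 participants per group achieves 95% power to detect differences among the means", by an F test at 5%. Take 0.30 as Cohen's f, with N = 40, m = 2 visits and correlation ρ = 0.5. The scale, m and ρ are assumptions, because the section does not give them.

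- λ = f² × N × m / (1 − ρ) = 0.09 × 40 × 2 / 0.5 = 14.4
- Degrees of freedom 1 and 38; critical F = 4.098; power = 0.959

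The stated 95% is reproduced. With two groups and two visits, the formula and degrees of freedom are the same for time and for group-by-time. The sample size therefore does not reveal which term the trial was designed around.

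**Inputs for the error check.** From the article: 20 per arm ("a minimum of 40 office-workers aged 40–64 years will be recruited, enrolled, and randomized (n = 20 per group"), two or three visits (Table 3), and α = 0.05. Assumed, because the article does not give them: ρ = 0.5 or 0.7, equal correlation between visits, a linear shared drift δ of 0 to 0.5 SD over 16 weeks, and no programme effect.

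**Rule simulated.** If any of the three F tests has p < 0.05, compare baseline with the last visit within each arm by a paired t test. Apply Bonferroni over the pairs of visits (1 pair for two visits, 3 for three).

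| Visits | ρ | Drift (SD) | Time term significant | Trigger met and training arm significant | Same, control arm not significant | Group-by-time significant |
|---|---|---|---|---|---|---|
| 2 | 0.5 | 0 | 5% | 3% | 3% | 5% |
| 2 | 0.5 | 0.2 | 24% | 11% | 9% | 5% |
| 2 | 0.5 | 0.5 | 87% | 55% | 24% | 5% |
| 2 | 0.7 | 0.2 | 36% | 17% | 13% | 5% |
| 2 | 0.7 | 0.5 | 98% | 78% | 17% | 5% |
| 3 | 0.5 | 0 | 5% | 1% | 1% | 5% |
| 3 | 0.5 | 0.2 | 18% | 5% | 4% | 5% |
| 3 | 0.5 | 0.5 | 80% | 36% | 22% | 5% |
| 3 | 0.7 | 0.2 | 28% | 8% | 7% | 5% |
| 3 | 0.7 | 0.5 | 96% | 61% | 24% | 5% |

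(100,000 simulated trials per row. Runs of 20,000 agree to within about one percentage point.)

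**Closed-form check, two visits.** The SD of change is √(2(1 − ρ)), which is 1.0 at ρ = 0.5 and 0.775 at ρ = 0.7. At δ = 0.5 and ρ = 0.7:

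- Time F test: λ = 40 × 0.25 / 0.6 = 16.67, power 0.978
- Paired t test in 20 people: noncentrality 0.5 × √20 / 0.775 = 2.89, power 0.782

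The second figure is an upper bound on the gated result, and the simulated 78% sits just below it.

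**With no drift.** At least one of three independent tests is significant with probability 1 − 0.95³ = 14.3%, and the simulation gives 14%. Even so, the training arm is then declared changed in only about 3% (two visits) or 1% (three visits).

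**After gating on group-by-time.** The gate opens in about 5% of null trials whatever the drift.

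**The case against.** A reader might infer that the plan will report a shared change as a programme effect, or that the control group plays no part in the conclusion. The article does not support either reading. It also plans inter-group comparisons, the planned ANOVA contains the interaction, it commits to CONSORT reporting, and it criticises studies without controls. The Data analysis section does speak of changes promoted by the exercise programme, but loose wording is not a decision rule.

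Other points on that side:

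- **What is triggered.** Strictly, only the Bonferroni tests are conditional; intra-group comparison belongs to the ANOVA's stated purpose. After a time effect, post hoc tests often pool the arms. The within-arm step simulated here is one permitted reading of intra-group comparison, not a specified procedure. This stands as a limit.
- **Trigger rates are not false-positive rates.** Under drift the time null is false, so the time column above is mostly power to detect a real common change. This stands, and the size is therefore taken from the training-arm column.
- **Drift is assumed.** The plan keeps the same testing staff, uses fixed morning windows, matches menstrual phase and sets a spirometry repeatability criterion. Samples are frozen for later assay, so a batch difference between visits is not established. Apart from blood pressure and BMI, eligibility sets no threshold on an outcome, which weakens an appeal to regression to the mean. These measures make drift less likely but do not exclude it.
- **Detail for an analysis plan.** Leaving a decisive term unnamed could be condensation. But the article does state the model, the trigger, the alpha and the post hoc test, and that stated rule is too wide.

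**Conclusion.** The point holds as a fault in the stated rule. The post hoc trigger is open to any ANOVA term, intra-group comparison is an explicit purpose, and nothing reserves the programme conclusion for the between-arm comparison of change. A significant training-arm result can therefore arise from a change common to both arms.

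The size rests on the assumed drift (0.2 to 0.5 SD) and correlation (0.5 to 0.7), and on reading the follow-up as pre-post tests within each arm. On that basis it is about 11 to 78% for two-visit outcomes and 5 to 61% for three-visit outcomes, against 5% for group-by-time. With no drift the rule does little harm. The article permits the misattribution but does not plan it. The wording should be corrected; the design itself is not undermined.

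**What to change.** Amend the Data analysis section to say three things:

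1. A programme effect is concluded only from the between-arm comparison of change. Name in advance either the group-by-time term or the between-arm contrast at week 16.
2. Bonferroni post hoc tests are run only when that comparison is significant. For outcomes measured at three visits they compare the arms at weeks 8 and 16. Blood and saliva have no week-8 sample, so for them group-by-time is itself the test and no post hoc step is needed.
3. Within-arm changes are presented as descriptive means with 95% confidence intervals and are not used to claim an effect.

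This takes a few sentences and needs no new data or participants. The cost is that within-arm p-values no longer count as evidence that the programme works. The change should be made before anyone sees outcome data by arm.

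### The Cohen's d bands have no trivial category and start 'medium' at 0.21, below the standard error of a between-group d with 20 per group, so chance results can readily be labelled 'medium'

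*Protocol article*

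**What the plan says.** The protocol article, Data analysis, states: "The magnitude of the global effect size will be calculated using Cohen’s effect size". It then sorts d into three bands, with values below 0.20 in the lowest: "0.20 (small), 0.21–0.79 (medium) and > 0.80 (large". The section does not say which comparison the effect size refers to (between groups, within group, or the interaction) or which SD divides it. The post hoc test is the only step expressly made conditional on a significant result. No interval for d is mentioned.

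The section also plans mean ± SD for all variables and a two-way repeated-measures ANOVA at the 5% level. Its separate scale for correlations attaches no label below 0.10.

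The size is fixed under Participants ("randomized (n = 20 per group") and under Estimated sample size, where 20% more are to be enrolled to cover dropouts.

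**The concern.** The lowest grade is already 'small', so an estimate of exactly zero is reported as a small effect. The next grade, 'medium', starts at 0.21 and runs to 0.79, so one word covers a nearly fourfold range. At this sample size, 0.21 is about two thirds of one standard error of a between-group d. The grade uses the point estimate only and takes no account of its precision.

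The article names a long list of primary measures: blood and salivary markers, blood pressure, spirometry and four questionnaires. If the programme did nothing, a substantial share of them could still carry the word 'medium'. That word is the plan's only stated rule for putting effect size into words, and the Discussion expects the results to inform clinical recommendations.

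**Working it through.** **The plan's own figure.** The article states: "For an effect size of 0.30, a sample size of 20 participants per group achieves 95% power". This reproduces as the group-by-time interaction in a repeated-measures ANOVA if 0.30 is read as Cohen's f, with two time points (m = 2) and an assumed pre-post correlation ρ = 0.5. The noncentrality is λ = f²·N·m/(1 − ρ) = 0.09 × 40 × 2/0.5 = 14.4 on 1 and 38 df. Power is 0.959, and the minimum N for 95% is 40. Read as d, 0.30 with 20 per group would give power of only 0.16. So the planning effect is not on the scale that the bands grade.

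**Inputs for the check.** The bands come from Data analysis and n = 20 per group from Participants. Assumptions: normal data, a true effect of zero, and d taken as the between-group difference over the pooled SD of the quantity compared.

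**Standard error.** SE(d) ≈ √(2/n) = √(2/20) = 0.316. Then 0.21/0.316 = 0.66.

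**Chance of each label when nothing works.** Under the null, d·√(n/2) follows t with 2n − 2 df, so P(|d| ≥ c) = 2·P(t > c·√(n/2)). For n = 20, √(n/2) = 3.162 and df = 38:

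| Cut c | P(\|d\| ≥ c) |
|---|---|
| 0.20 | 0.531 |
| 0.21 | 0.511 |
| 0.50 | 0.122 |
| 0.80 | 0.016 |

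By symmetry, the favourable direction alone gives 0.511/2 = 0.26 at 0.21. Nearly all chance labels above 'small' are 'medium'; 'large' is under 2%. The median null |d| is 0.215, which lies inside the 'medium' band.

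**Other group sizes.** P(|d| ≥ 0.21) is 0.56 with 16 per group. It is 0.47 with 24 per group, which is what a 20% increase gives (40 × 1.2 = 48, halved).

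**Other definitions of d, 20 per group.**
- Difference in change over baseline SD, with SE = √(4(1 − ρ)/n) and a normal approximation at 0.21: 0.51 for ρ = 0.5, 0.39 for ρ = 0.7, 0.14 for ρ = 0.9.
- Within-group change over change SD: 0.36 at 0.21 (0.38 at 0.20).
- d converted from the interaction partial eta-squared: 0.54 with two time points and 0.69 with three, both at 0.20 (0.52 and 0.66 at 0.21).

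The range is therefore about 14% to 69%. The values of ρ are assumptions; the article gives none.

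**Where significance begins.** In a simple two-group comparison the critical |d| is t(0.975, 38)/√10 = 0.640. The non-significant share of the 'medium' band is (0.64 − 0.21)/(0.79 − 0.21) = 0.43/0.58 = 0.74. At d = 0.21 the 95% CI is 0.21 ± 1.96·√(0.1 + 0.21²/80), which is −0.41 to 0.83, with p = 0.51.

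**The case against.** The strongest reply is that the label is only a descriptive adjective. Inference rests on the ANOVA, the post hoc tests and the 5% level; the grade triggers no decision, and the type I error is untouched. Mean ± SD and the numerical d are also planned, so readers can see the size for themselves. All of this stands, and it limits the point to description and reading.

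A reader might infer that about half of all outcomes will be called medium or large under no effect, and that this will look like broad benefit. The documents do not support that as a flat statement. The article leaves d undefined, the rate depends heavily on the definition, and about half of any chance labels would favour the control group. Nor can one say that the grade is the only information on size.

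It can also be said that grading may be meant only for significant outcomes, because the effect-size sentence follows the one on post hoc testing. That reading is possible, but the text does not state it. The gaps between bands are slight: to two decimals only 0.20 and 0.80 are unassigned, and the printed symbol before 0.20 may mean 'less than or equal to'.

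Finally, a missing CI for d could be detail that an article leaves to a fuller plan. The point therefore rests on the bands that the article does fix; the CI is part of the remedy.

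**Conclusion.** The point holds as a reporting flaw in a rule that the article itself states. Under every definition of d, zero is graded 'small', no value can be called trivial, and 'medium' starts at 0.21.

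The size of the consequence is conditional. It is about 51% of outcomes at |d| ≥ 0.21 (about 26% in the favourable direction) if d is between groups, standardised by the SD of the compared quantity, with normal data and 20 per group. Across other definitions it is about 14% to 69%. These are expected shares; correlation between outcomes changes their spread, not their mean. The three-quarters figure for the non-significant part of the 'medium' band applies to a simple two-group comparison, not to the planned repeated-measures ANOVA.

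**What to change.** In Data analysis, state that d is the between-group difference (in change, or baseline-adjusted) and name its standardiser, for example the pooled baseline SD. Report d with its 95% CI for every outcome. Replace the bands with contiguous ones that include a trivial category and do not start 'medium' at 0.21. One example is trivial below 0.20, small 0.20–0.49, medium 0.50–0.79 and large from 0.80. In the base case this lowers the chance rate of 'medium or large' from about 51% to about 12%. It does not remove it, so any verbal grade should always appear beside its interval. Withholding every grade when the interval includes zero is debatable, because it turns a description of size into a significance test; it is not needed here.

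The cost is a short rewording and one extra column in the results tables. The downside is that fewer outcomes will be called 'medium'.

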## Abstract

**Background:**

Both physical inactivity and sedentary behavior are considered modifiable risk factors for chronic diseases and all-cause mortality. Adult office-workers spend most of their working day in sedentary behaviors, so they are particularly at high risk of developed chronic diseases (e.g., cardiovascular diseases, metabolic disorders like diabetes mellitus, …). It seems important to promote behavioral changes that could prevent or delay metabolic disease development. Evidence supports the use of exercise programs, however, to date there are several knowledge gaps and inconsistencies in the literature regarding the effects of Combined Training (i.e., aerobic plus resistance training) in sedentary healthy adults. This paper outlines an RCT designed to evaluate the effects of a 16-week combined training program on biochemical and immune markers of metabolic disease, lung function, salivary stress hormones and subjective quality of life (primary outcomes), as well as on body composition and physical fitness (secondary outcomes) in sedentary middle-aged office-workers. Furthermore, we aimed to assess the associations between the changes promoted by the exercise program and the different variables studied.

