*Assessment of dietary intake*. Dietary habits will be assessed using a semi-quantitative Food Frequency Questionnaire (FFQ) [98], based on the previous 12 months. The FFQ was previously adapted for the Portuguese population [99, 100]. This instrument contains 82 food items, including 9 possible frequency responses, ranging from “never” to “six or more times per day” [100]. Any foods not reported in the FFQ but eaten regularly can be registered in an open-ended section [100]. To obtain nutrient intake, the frequency of consumption of each food item will be multiplied by the respective standard average portion (in grams), and by a seasonal variation factor for food consumed in specific seasons (0.25 are considered the average seasonality of three months) [100]. The conversion of food into nutrients will be performed using the software program Food Processor Plus (version 5.0, ESHA Research, Salem, OR), based on values from the US Department of Agriculture and from the composition of typical Portuguese foods that were included in this software [100, 101].

*Health*, *demographic*, *and lifestyle data*. Sociodemographic characteristics such as chronological age, gender, education degree, and marital status will be collected to characterize the sample and to adjust models. Health information will include past and current diseases (acute and/or chronic), medication, family history of metabolic diseases, dementia, or cognitive impairment. The “Pittsburg Sleep Quality Index” (PSQI) questionnaire will also be applied, before and after the trial, to assess subjective sleep quality over the previous month [102, 103]. Lifestyle information will include smoking history, consumption of alcoholic drinks, substance abuse and supplement use.

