## Discussion

This project will allow us to investigate the potential effects of a 16-week CT program on several health indicators, namely: biochemical and immune markers of metabolic disease, body composition, physical fitness, lung function, salivary stress hormones and subjective quality of life. Furthermore, we will assess the associations between the changes promoted by the exercise intervention and the different variables studied. Thus, based on results of other studies with a vast breadth of populations or co-morbidities included [32, 39–41], we will check the hypothetical premise that 16-weeks of CT program, carried out in a moderate to vigorous intensity, can improve the inflammatory status, insulin resistance and other metabolic risk factors in sedentary office workers. We also look at the hypothetical premise that the CT program will improve lung function [20, 21, 44], stress levels and subjective quality of life [24]. Moreover, we will check the premise that some changes promoted by the exercise intervention are associated with different variables studied, for example, evidence suggests that most of the benefits of exercise on the inflammatory cytokines seem to be mediated by body composition changes [11, 32]. Also, a better lung function could be associated with a decrease in pro-inflammatory cytokines (induced by exercise) [106, 107]. This research project involves a multi-disciplinary approach and should be seen as an original and relevant contribution to understanding the potential role of a specific mode of exercise in improving metabolic risk markers, lung function, stress, and quality of life in sedentary adults. The results of this study will provide important insights for clinical recommendations and for the optimization of prevention and treatment strategies to combat metabolic diseases in sedentary adults. In addition to these indicators, de Vries et al. [108] have concluded that exercise may also play an important role in reducing work-related fatigue and improving a set of indicators of employee well-being, such as work ability, cognitive status/ function, and sleep quality. The results of this project may also help to develop further theories and models explaining CT effects in sedentary adults.

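### The correlations between changes are unadjusted and the analysis set is not stated; if the arms are pooled, two outcomes that both respond to exercise can appear linked without any within-arm association

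*Protocol article*

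**What the plan says.** The Abstract sets out a further aim: "we aimed to assess the associations between the changes promoted by the exercise program and the different variables studied". The Introduction repeats it almost word for word. The Data analysis section gives the aim one method. It takes "The bivariate associations between the changes promoted by the exercise program and the different variables studied" and says these "will be assessed by Spearman’s rank and Pearson’s coefficients". The coefficients are then graded in bands of r and judged against the general rule, "Significance level set at *p* ≤ 0.05".

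That section mentions no partial correlation, no regression, no arm term and no baseline term. The only mention of adjustment is under Supportive measures, where sociodemographic data "will be collected to characterize the sample and to adjust models". Neither arm nor baseline outcome values are among those data, and Data analysis names no adjusted model.

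No section says whether the correlations use all participants or only those in the combined training arm.

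The Discussion gives examples of the links of interest. One is earlier evidence that "most of the benefits of exercise on the inflammatory cytokines seem to be mediated by body composition changes". Another is a possible link between better lung function and lower pro-inflammatory cytokines.

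**The concern.** The trial expects exercise to improve many outcomes together: inflammation, insulin resistance, lung function, stress and quality of life. Suppose exercise lowers both body fat and a cytokine, and the two changes are unrelated from person to person within each arm. Across the pooled sample, trained participants will tend to show both changes and controls neither, so the two changes correlate. That correlation only shows that both outcomes responded to allocation. An unadjusted coefficient cannot tell it apart from a link between individuals, and the link between individuals is what the aim is about.

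Because the analysis set is open, the text allows two analyses with different properties: one exposed to this artefact, the other free of it but imprecise. The choice could be made after the data are seen.

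A further aim of the trial is at stake. The randomised comparison of the arms is not affected.

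**Working it through.** **Inputs.** From the protocol article: 1:1 allocation, 20 per group, significance at 0.05 (taken as two-sided for r), effect size 0.30 with an F test and 95% power. Assumptions: normal change scores, equal variances in the arms, no dropout, and no within-arm correlation between the two changes.

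**1. The plan's own figure.** Estimated sample size states: "For an effect size of 0.30, a sample size of 20 participants per group achieves 95% power". Reading 0.30 as Cohen's f for a group-by-time interaction with m = 2 measurements and a correlation of ρ = 0.5 between them (m and ρ are my assumptions; the article gives neither):

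λ = N·f²·m/(1 − ρ) = 40 × 0.09 × 2/0.5 = 14.4

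This gives power 0.959, and 40 is the smallest even total that reaches 95%, so the figure reproduces. With m = 3 and ρ = 0.5 the minimum would be 32, so the match depends on these assumptions.

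**2. The same effect on the change scale.** Let d be the arm difference in mean change divided by the within-arm SD of change. For two equal arms λ = N·d²/4, so d² = 14.4 × 4/40 = 1.44 and d = 1.2.

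**3. Correlation produced by pooling.** With no within-arm correlation and equal arms:

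r = (d₁d₂/4) / √[(1 + d₁²/4)(1 + d₂²/4)]

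When d₁ = d₂ = d this is d²/(d² + 4). For d = 1.2: 1.44/5.44 = 0.265. At n = 40 a coefficient is significant when |r| is above 0.312.

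**4. False-positive rates.** From 20,000 simulated trials per row, 20 per arm:

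| Effect on the two outcomes | Expected pooled r | Pooled, Pearson | Pooled, Spearman | Adjusted for arm | Exercise arm only |
|---|---|---|---|---|---|
| 0.3 and 0.3 | 0.022 | 5.1% | 4.9% | 4.6% | 4.8% |
| 0.6 and 0.6 | 0.083 | 8.3% | 8.2% | 5.2% | 5.0% |
| 0.8 and 0.8 | 0.138 | 13.3% | 13.3% | 4.7% | 4.9% |
| 1.0 and 1.0 | 0.200 | 24.2% | 24.6% | 4.8% | 5.1% |
| 1.2 and 1.2 | 0.265 | 39.9% | 41.3% | 5.4% | 5.1% |
| 1.2 and 0.6 | 0.148 | 14.9% | 15.2% | 4.9% | 5.3% |
| 1.2 and 0 | 0.000 | 5.1% | 5.0% | 5.0% | 4.9% |

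With 24 per arm (20% over-enrolment, 40 × 1.2 = 48, no losses), d = 1.2 for both outcomes gives 46.7% for pooled Pearson.

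**5. Exercise arm alone.** The artefact is absent, but at n = 20 significance needs |r| above 0.444. For an observed r of 0.30, Fisher's z is 0.310 with standard error 1/√17 = 0.243. The limits are 0.310 ± 1.96 × 0.243, that is -0.166 to 0.785, or -0.16 to 0.66 back on the r scale.

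**6. Baseline.** Assume no exercise effect, a correlation r_b between the two baselines, and a retest correlation ρ for each outcome. Regression to the mean then gives the two changes a correlation of r_b(1 − ρ)/2. For r_b from 0 to 0.5 and ρ from 0.5 to 0.7 this runs from 0 to 0.5 × 0.5/2 = 0.125 (simulated 0.124). The simulated rejection rate at n = 40 is 5% to 12%.

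**The case against.** The strongest reply is that pooling is never stated and is arguably the less natural reading. Controls do no exercise training during the trial, so changes brought about by the programme occur only in the training arm, and there the artefact cannot arise. This stands. A reader might infer that the plan pools the arms and so will report false links; the article supports only the conditional statement.

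Second, the effect is limited even under pooling. At d = 1.2 for both outcomes about 60% of unrelated pairs would still not be flagged, and the expected r of 0.265 falls in the plan's lowest band (0.10 to 0.30). Both outcomes must respond strongly. This also stands: pairs can look linked; it does not follow that they will.

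Third, a reader might infer from the Discussion that a mediation analysis is planned. It is not. The mediation wording describes earlier literature, and the trial's own premise is worded as association.

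Fourth, a condensed article may leave detail to a full analysis plan. That covers the list of pairs and the reporting of confidence intervals, so neither is part of this point. It does not cover the method, which the article fixes as bivariate and unadjusted.

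Fifth, an arm-adjusted analysis of everyone estimates a common within-arm slope, mixing ordinary fluctuation in controls with response to training. An analysis of the training arm alone may suit the aim better. That is a fair choice for the investigators, provided it is stated.

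**Conclusion.** The point holds in conditional form. The article fixes unadjusted bivariate coefficients for a stated aim and leaves the analysis set open. If the arms are pooled, the false-positive rate for two unrelated outcomes that respond equally rises from about 5% at d = 0.3 to about 40% at d = 1.2, against about 5% after adjustment for arm. The upper figure corresponds to the trial's own effect size only if two measurements and ρ = 0.5 are assumed, and only if both outcomes reach it. With one responding outcome there is no inflation.

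If only the training arm is used, the weakness is low precision, not a false link due to allocation. Omitting baseline adds a spurious r of about 0 to 0.12 between two changes under the assumed correlations. That mechanism is separate from the shared response to exercise.

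The documents do not support saying that the conclusion on this aim would be wrong. They support saying that it could be, and that the text does not prevent it. This should be changed, but it does not touch the main comparison of the arms.

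**What to change.** In Data analysis, state which participants enter the correlations.

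- If both arms are used, replace the bivariate coefficients with partial correlations, or a regression of one change on the other, adjusted for arm and for the baseline values of both variables.
- If only the training arm is used, say so, and adjust for the two baseline values.

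In either case keep describing the results as associations. They cannot separate mediation from two independent effects of exercise.

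The data are already collected and the change takes a few sentences. The cost is a few degrees of freedom: with 40 participants, from 40 − 2 = 38 to 40 − 2 − 3 = 35; with 20 in the training arm, from 20 − 2 = 18 to 20 − 2 − 2 = 16.
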